### Intervention and Comparators

As previously mentioned, the telerehabilitation intervention program will be delivered through the AI telerehabilitation platform designed and marketed by WizeCare [28]. WizeCare is a medium-sized digital health company that has developed an innovative solution for remote physical therapy and exercise training at home. The system includes over 800 exercises that encompass strength, coordination, and flexibility, targeting the lower and upper body and core muscle groups and joints, enabling the therapist to create a tailored exercise program. Moreover, the system includes a technology called MoveAI (patent no. US 11,636,777 B2), which identifies, tracks, and analyzes the user’s movement without requiring customized sensors but instead using the camera available on a smartphone, tablet, or PC. This will provide the user (ie, patient) with immediate feedback and guidance. Figure 2 illustrates key features of the telerehabilitation digital platform. The system is safe and has been confirmed by several security certificates of the highest standard (ISO/IEC 27001:2013; ISO27799:2016; AMAR [Israeli standard]: 29460001). Additional data on adherence and compliance will be collected via the WizeCare telerehabilitation platform.

**Figure 2 figure2:**
[figure not shown]
Key elements of the telerehabilitation digital platform.

The telerehabilitation exercise intervention program will comprise a 10-week, physiotherapist-prescribed, evidence-based, individualized exercise program based on the exercise guidelines for people with MS and the physiotherapist’s clinical reasoning [34]. Eligible participants will receive tailored exercise instructions, which will include performing 8 to 10 exercises in accordance with their abilities and functional needs. Following the first week of training, the participant will be contacted by a physical therapist (via video or audio chat through the system) to monitor participation, progress, and adverse events. Participants in the telerehabilitation group will be compared to those in usual care. Since the term “usual care” is broad, particularly across countries, and physical activity participation varies, participants in both groups will provide weekly information about their physical activity based on the FITT-VP (frequency, intensity, time, type, volume, and progression) principles [35]. To measure adherence, all participants will receive a diary and be requested to log their exercises and submit reports weekly. The report submission will be monitored weekly with a phone call by a physical therapist.

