### Methodology, Approach, and Study Population

The different WPs of the research project and timeline are presented in Figure 1 and Table 1. The first phase of this project will examine the system usability and feasibility of an innovative advanced telerehabilitation system in people with MS (WP2). The system usability and feasibility study will be conducted in each participating country (Israel, Italy, Ireland, and Denmark) with a small group of people with MS (n=10 per center) with varying disability. Participants will be recruited according to the following criteria: aged 18 years or older; confirmed diagnosis of MS based on the McDonald criteria [30] (both relapsing-remitting and progressive MS); an Expanded Disability Status Scale (EDSS) score of 2.5-6.5; willing to travel to the local study site for the evaluation sessions; and internet service, and having a device (eg, smartphone, tablet, or PC) equipped with a camera that meets the technical specifications recommended by the telerehabilitation system manufacturer. Individuals who have had a documented relapse during the past 3 months will be excluded, as will those who are unable to follow simple instructions.

Following assessment and exercise prescription, participants will complete an exercise program delivered by the telerehabilitation system. The short-term program will include 8 exercise training sessions (45- to 60-minute sessions twice weekly for 4 weeks). The amount of training throughout the short-term program will be sufficient for collecting data and taking note of the safety, usability, and feasibility of the advanced rehabilitation technologies [31]. The primary outcome measure of WP2 will be collected at the end of the short-term telerehabilitation exercise program with the Telehealth Usability Questionnaire (TUQ) [32], a solid, robust, and versatile tool used to measure the quality of the telehealth system’s interaction and services. In addition, qualitative data will be collected through semistructured interviews with key stakeholders (people with MS and therapists) and analyzed thematically.

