In parallel with the system feasibility and usability study, we plan to develop and psychometrically test a set of remote balance and functional mobility tests delivered via the telerehabilitation system (WP3). We will adapt and manualize 5 remote mobility tests that are collected through the telerehabilitation system: the 30-second sit-to-stand (30STS) test, timed-up-and-go (TUG) test, functional reach test (FRT), 20-second single-leg stance (20SLS) test, and the Short Physical Performance Battery (SPPB). The SPPB includes the following tests: side-by-side stand (10 seconds), semitandem stand (10 seconds), tandem stand (10 seconds), a gait speed test over 3 meters, and a 5-time repeated chair stand test. Upon completion of the developmental phase, we will conduct a test-retest reliability study for in-person and telehealth data capture and a criterion validity study comparing telehealth and in-person data with 15 people with MS (EDSS 2.5-6.5) at each site (n=60).

To examine the efficacy of the advanced telerehabilitation solution for people with MS, we propose an international feasibility multicenter RCT (WP4). We will include a target sample of 24 participants per country (in 4 countries; 96 participants in total) based on the stepped rule of thumb proposed by Whitehead et al [33], who estimated the optimal sample size for an early-stage/pilot RCT to be 24. Importantly, as the results may differ across countries, we consider each country an individual site for the feasibility RCT. Statistical analysis will be performed for the total group and each country separately. The participants will be randomly allocated (individual randomization) into one of two groups: (1) home-based telerehabilitation exercise training via the WizeCare platform [28] or (2) usual care. The sample criteria for the feasibility multicenter RCT will be the same as those for WP2.

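### Adverse-event monitoring in the WP4 trial is assigned only to a platform contact in the telerehabilitation arm, so as written harms would be ascertained unequally between arms

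*Protocol article*

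**What the plan says.** All references are to the protocol article.

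- **Adverse-event contact.** The Intervention and Comparators section (text after Figure 2) describes a 10-week telerehabilitation programme. Within that description, and timed as "Following the first week of training", it states that "the participant will be contacted by a physical therapist (via video or audio chat through the system) to monitor participation, progress, and adverse events". The term adverse events appears nowhere else in the article.
- **Arms.** Methodology, Approach, and Study Population randomizes individuals to home-based training on the platform or to usual care. No platform use is stated for usual care.
- **Contacts stated for everyone.** The Intervention and Comparators section says that "participants in both groups will provide weekly information about their physical activity". It continues: "To measure adherence, all participants will receive a diary and be requested to log their exercises and submit reports weekly". The next sentence is "The report submission will be monitored weekly with a phone call by a physical therapist".
- **Safety elsewhere.** Methodology, Approach, and Study Population mentions "taking note of the safety, usability, and feasibility of the advanced rehabilitation technologies", but for WP2, a 4-week study with no control group described. Outcome Measures for the Feasibility Multicenter RCT lists no adverse-event outcome, and Data Analysis and Statistical Plan describes no analysis of harms.

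**The concern.** A comparison of harms between randomized arms is fair only if events are looked for in the same way, equally often, in both. Here the one contact with an adverse-event purpose belongs to one arm, while the contacts that reach both arms are given other purposes. If the sites follow the text, a fall or injury in the telerehabilitation arm has a therapist asking about it. The same event in a usual-care participant is recorded only if it is volunteered or comes up by chance.

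This matters because WP4 tests home exercise in people with EDSS scores from 2.5 to 6.5, and the Discussion says the results should inform a fully powered RCT. WP4 is also the only randomized part of the project, so it is the only place where event rates with and without the system can be set side by side. The Intervention and Comparators section does call the system safe, but supports this with data-security certificates, not clinical data.

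**Working it through.** **Step 1. Set the stated contacts side by side.**

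| Contact | Telerehabilitation | Usual care | Stated purpose |
|---|---|---|---|
| Therapist video or audio chat through the platform, after week 1 | Yes | No platform use stated | Participation, progress, adverse events |
| Weekly physical activity information | Yes | Yes | Physical activity |
| Weekly diary and report | Yes | Yes | Adherence |
| Weekly therapist phone call | Yes | Yes, by inference | Report submission |

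The call is read as covering both arms because it follows directly on the sentence giving all participants a diary and weekly report. The authors say so explicitly where they want a procedure in both arms. They do not do so for adverse events.

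**Step 2. Does the result depend on how often the platform contact occurs?** The text does not settle whether there is one contact after week 1 or a series starting then. A single contact would leave the later weeks of the programme without a stated check. A continuing series would cover them, but only in the telerehabilitation arm. The arms differ on either reading.

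**Step 3. Direction and possible size.** The article gives no event rate, detection probability or allocation ratio, so there is no figure to reproduce and no size to derive. The following is an illustration under stated assumptions.

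- Recorded risk = true risk × detection probability.
- With equal true risk in both arms, recorded risk ratio = detection (telerehabilitation) ÷ detection (usual care). The true risk cancels.
- Detection is assumed to be 90% with telerehabilitation and 90%, 60% or 30% with usual care. This gives 0.9/0.9 = 1.0, 0.9/0.6 = 1.5 and 0.9/0.3 = 3.0.
- The article's total is 24 × 4 = 96. Equal allocation is an assumption and gives 96/2 = 48 per arm.

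Expected participants with a recorded event (48 × true risk × detection):

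| Assumed true risk | Telerehabilitation, 90% | Usual care, 60% | Usual care, 30% |
|---|---|---|---|
| 10% | 4.3 | 2.9 | 1.4 |
| 20% | 8.6 | 5.8 | 2.9 |
| 30% | 13.0 | 8.6 | 4.3 |

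For example, at 20%: 48 × 0.20 × 0.90 = 8.6 against 48 × 0.20 × 0.60 = 5.8. The whole difference comes from detection. The direction follows from more active questioning in one arm; the amount depends entirely on the assumed detection values.

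**The case against.** The strongest reply is that this is a condensed article. Definitions, collection and reporting of adverse events commonly sit in the full protocol, which is not shown. The SPIRIT checklist is an appendix that is also not shown, and the WP4 ethics applications are still to be submitted. A therapist checking on someone who has started a home programme may simply be part of delivering the intervention, and nothing in the text forbids recording events in usual care. This part stands: a reader might infer that adverse events are monitored by no other route, or that harms cannot be compared at all, and the article does not support either. The weekly call, the post-intervention assessment and the health-service-use data are all routes by which control events could come to light.

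Three further points also stand.

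- A reader might infer one contact in ten weeks. The wording is open, and the Discussion promises therapist follow-up and remote use tracking.
- A reader might infer that a go/no-go decision would be biased. No such rule is stated.
- No between-arm comparison of harms appears among the objectives, research questions, outcomes or analyses, so no stated analysis is undermined.

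The reply does not remove the point itself, because the article is not merely silent. It gives each contact a mode and a purpose, and attaches adverse events to the one that usual care cannot receive. A full protocol may add a common procedure, but the published text as it stands describes an unequal one.

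**Conclusion.** The point holds in a limited form. As written, adverse events would be actively asked about in the telerehabilitation arm and not in usual care, so harms reported by arm would be ascertained unequally, with a likely spurious excess in the telerehabilitation arm. This holds whether the platform contact is single or continuing.

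It rests on three readings of the text: that the adverse-event contact belongs to the telerehabilitation arm, that usual-care participants do not use the platform, and that the weekly call is limited to its stated purpose. It also assumes that no common procedure in the full protocol overrides the article.

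The size cannot be computed from the document; the ratios of 1.5 and 3.0 only show what the assumed detection rates imply. The correction is worth making before WP4 starts, but the point does not invalidate the design or any stated analysis.

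**What to change.** 1. At the weekly therapist phone call, ask the same scripted adverse-event questions in both arms, with the same wording and recall period, and state explicitly that the call covers both arms.
2. Report events by arm from that common source.
3. List events detected through the platform contact separately, and keep them out of any between-arm summary. They remain useful for describing safety within the telerehabilitation arm.
4. State whether the platform contact after week 1 is made once or continues.
5. If the full protocol already contains a common adverse-event procedure, align the Intervention and Comparators text with it; a sentence would then be enough.

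The cost is a short addition to the call script, a form to record the answers, and slightly longer calls. No extra contacts or staff are needed. By the article's own timetable the WP4 ethics applications are still to be submitted and the trial is planned for January 2026, so the change can be made before enrolment. A common source does not remove every difference, since participants know their allocation and those also contacted through the platform may recall more, but it removes the difference that is built into the procedure.

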### Outcome Measures for the Feasibility Multicenter RCT

The outcome measures for WP4 will include the 30STS [36] (primary outcome), SPPB [37], 6-minute walk test (6MWT) [38], timed 25-foot walk test (T25FWT) [39], mini-BESTest (balance) [40], FRT [41], and a self-report questionnaire, the 12-item MS Walking Scale (MSWS-12) [42]. In accordance with the project’s secondary aims, we will examine the impact of the intervention programs on mood (ie, depression and anxiety with the State-Trait Anxiety Inventory [STAI] [43] and Quick Inventory of Depression Symptomology [QIDS] [44]), quality of life (EQ-5D-5L [45]) and the impact of MS (29-question Multiple Sclerosis Impact Scale; MSIS-29 [46]).

All outcome measures will be collected at baseline (at the initiation of the intervention program), and after the intervention period’s completion. Assessors (physical therapists) will be blinded to group allocation, and patient report outcomes will be collected using an online form. Other significant disease-related factors collected solely at baseline (together with demographic and relevant clinical information) will include perceived fatigue (Modified Fatigue Impact Scale; MFIS [47]) and cognition (Symbol Digit Modality Test; SDMT [48]). Additionally, we will collect baseline information on digital literacy, which may confound the intervention’s effectiveness. All outcome measures used for the study have been validated in people with MS and are recommended for rehabilitation and clinical trials.

### Data Analysis and Statistical Plan

Each research question is addressed through specific outcome measures. For RQ1, usability and feasibility will be assessed via the TUQ, adherence rates, dropout rates, and stakeholder interviews, with qualitative data analyzed thematically. RQ2 involves psychometric evaluation of remote assessments (e.g., SPPB, STS, and TUG) using intraclass correlation coefficients for test-retest reliability and Pearson correlations to compare remote and in-person scores. RQ3 and RQ4 outcomes (eg, 30STS, MSWS-12, EQ-5D-5L, STAI, and QIDS) will be analyzed using linear mixed models to assess within- and between-group effects over time. The primary analysis will follow an intention-to-treat principle, including all randomized participants in the groups to which they were originally assigned, regardless of adherence to the intervention protocol. A per-protocol analysis may be conducted as a secondary exploratory analysis. Missing data will be addressed using multiple imputation, assuming data are missing at random, and sensitivity analyses will be performed to assess the robustness of results.

As part of RQ5, the study also incorporates a comprehensive economic evaluation of the telerehabilitation system, which complements the clinical analyses and addresses a critical gap in MS rehabilitation research. A cost-utility analysis will be conducted to compare the telerehabilitation intervention and usual care, using incremental cost-effectiveness ratios derived from health care service use data and EQ-5D-5L–based quality-adjusted life years. Cost data will include implementation, infrastructure, maintenance, training, support services, and any differences in health service use or patient-reported outcomes. These data will be collected alongside the RCT to ensure alignment between clinical effectiveness and economic impact.

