**Methods:**

The PLATINUMS project begins with working package (WP) 1, focusing on obtaining ethical approval and recruiting staff. Following this, WP2 involves a 4-week system feasibility and usability study (n=40) to assess and refine the digital platform. WP3 comprises a validity study (n=60) to evaluate remote mobility tests via the system, such as the Short Physical Performance Battery (SPPB), functional reach, and sit-to-stand tests, to ensure their reliability for use in WP4, the feasibility multicenter randomized controlled trial (RCT). The 10-week multicenter feasibility RCT will be conducted in MS centers across Denmark, Ireland, Israel, and Italy, with 96 participants varying in disability levels. The primary objective is to evaluate the efficacy of the AI-powered telerehabilitation system on mobility outcomes compared to usual care. Finally, WP5 will assess the cost-effectiveness of the telerehabilitation system by analyzing implementation costs, adherence, and use of health care. The PLATINUMS project aims to revolutionize exercise therapy for people with MS by demonstrating the feasibility, validity, and preliminary efficacy of the AI-driven telerehabilitation system. This approach addresses barriers such as accessibility, privacy, and standardization while promoting patient and therapist acceptance.

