**Figure 1 figure1:**
[figure not shown]
PLATINUMS (Implementation of an Advanced Telerehabilitation Solution for People With Multiple Sclerosis) project overview based on working packages (WPs). DMSH: Danish Multiple Sclerosis Hospitals; FAIR: findable, accessible, interoperable, and reusable; RCT: randomized controlled trial; TAU: Tel Aviv University; UC: University of Cagliari; UL: University of Limerick.

**Table 1 table1:** PLATINUMS (Implementation of an Advanced Telerehabilitation Solution for People With Multiple Sclerosis) Gantt chart describing each working package (WP) and task (T).

		Year 1					Year 2					Year 3			
		Q1	Q2	Q3	Q4	Q5		Q6	Q7	Q8	Q9		Q10	Q11	Q12
**WP1: Ethical approval, staff recruitment**		✓													
**WP2: International usability and feasibility study of the telerehabilitation system**			✓	✓	✓	✓									
	T2.1. Installation of the telerehabilitation system, including private data security and cloud data management		✓												
	T2.2. Harmonization between staff members operating the telerehabilitation system and intervention program		✓												
	T2.3. Testing the system on a small group of participants for feasibility (patient/therapist), integrity, security, and proper transfer of data			✓	✓	✓									
**WP3: Development and validation study of balance and mobility functional tests delivered remotely**			✓	✓	✓	✓		✓							
	T3.1. Development of mobility assessment tests to be delivered remotely via the telerehabilitation system		✓	✓											
	T3.2. Establishing reliability and validity of the remote mobility tests			✓	✓	✓		✓							
	T3.3. Developing standardized instructions and training materials							✓							
**WP4: Efficacy study of the telerehabilitation study via a pilot multicenter RCT^a^**								✓	✓	✓	✓		✓	✓	
	T4.1. Coordination between staff members operating the intervention programs and blind assessors on all procedures related with the outcome measures							✓							
	T4.2. Implementation of intervention programs							✓	✓	✓	✓		✓		
	T4.4. Data analysis of remote and clinical outcome measures												✓	✓	
	T4.5. Assessing adherence to and satisfaction with (among participants/therapists) the telerehabilitation intervention program												✓	✓	
**WP5: Economic evaluation of the telerehabilitation system**								✓	✓	✓	✓		✓	✓	
	T5.1. Identifying the perspective of the economic evaluation and finalizing the specific study questions in terms of economics							✓							

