### Research and Innovation Questions

This innovative project will include 5 key research questions (RQs), which we propose will fill in the gaps in our current knowledge.

RQ1 (WP2) is as follows: In people with MS, what is the usability and feasibility of an advanced telerehabilitation system in facilitating remote exercise training? Qualitative and quantitative measures will be used to evaluate the usability and feasibility of the telerehabilitation system in 4 countries. Following necessary system upgrades and adaptations, findings will be incorporated into the feasibility multicenter RCT (WP4). Based on data from other patient populations, we hypothesize that the innovative telerehabilitation system will score highly for usability and feasibility among the participants with MS.

RQ2 (WP3) is as follows: In people with MS, are scores provided by clinical mobility tests obtained via tele-rehabilitation valid and reliable? Evidence for remote mobility evaluation does not currently exist for people with MS. We will evaluate 5 tests developed from commonly used clinical measures. We hypothesize that innovative remote mobility tests will demonstrate good-to-excellent validity and reliability.

RQ3 (WP4) is as follows: In people with MS, is a large multicenter RCT possible, and can it show preliminary efficacy of an individualized exercise program delivered via telerehabilitation to improve mobility compared with in-person physical therapy? An international pragmatic multicenter feasibility RCT will be conducted to compare the effectiveness of delivering the individual exercise program via telerehabilitation versus in person by a physiotherapist. We hypothesize that both exercise intervention programs will improve mobility in people with MS; however, nonsignificant differences in mobility outcome measures between groups (telerehabilitation vs usual care) will be demonstrated.

RQ4 (WP4) is as follows: In people with MS, does an individualized exercise program delivered via telerehabilitation have a comparable effect on mood and quality of life (QoL) compared with standard physical therapy (facility based)? This RQ will be answered in the planned international multicenter feasibility RCT, preceded by a feasibility and usability study. Consequently, our hypothesis is that mood and QoL will be improved in participants whose symptoms are significant at baseline.

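### WP3 compares remote with in-person scores by Pearson correlation alone, which cannot show whether the two modes agree

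*Protocol article*

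**What the plan says.** The protocol article describes WP3 in two parts (Methodology, Approach, and Study Population). One is reliability: "we will conduct a test-retest reliability study for in-person and telehealth data capture". The other is validity: "a criterion validity study comparing telehealth and in-person data", with 15 people at each of four sites. Five tests are to be adapted for remote delivery: 30-second sit-to-stand (30STS), timed-up-and-go (TUG), functional reach (FRT), 20-second single-leg stance, and the Short Physical Performance Battery (SPPB).

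The Data Analysis and Statistical Plan gives each part its own statistic. Reliability is assessed "using intraclass correlation coefficients for test-retest reliability". Validity is assessed by "Pearson correlations to compare remote and in-person scores". The article names no mean difference, limits of agreement, concordance coefficient or cross-mode ICC.

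The expected result is stated without a numerical threshold: "We hypothesize that innovative remote mobility tests will demonstrate good-to-excellent validity and reliability" (Research and Innovation Questions, RQ2). The Methods paragraph of the Abstract links WP3 to the randomised trial, since the remote tests are evaluated "to ensure their reliability for use in WP4". Task T4.4 in Table 1 reads "Data analysis of remote and clinical outcome measures".

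**The concern.** The remote tests are adaptations of established clinical tests. A remote 30STS counts repetitions, a remote TUG gives seconds, and a remote SPPB gives points on the same scale as the in-person version. When two methods report the same quantity in the same unit, the useful question is how far apart they are in the same person. Correlation answers a different question: whether people are ordered and spaced alike.

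A remote test that misses two repetitions in everyone, or adds a fixed delay to every timing, keeps a perfect record on Pearson r. The test-retest ICC does not fill the gap, because it compares a mode with itself.

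At stake is the RQ2 conclusion. A high r would be reported as support for validity although remote scores might be systematically off. That would mislead anyone who reads a remote score against in-person norms, pools scores from both modes, or follows a person across modes. 30STS (named as the WP4 primary outcome), SPPB and FRT are both remote tests in WP3 and outcomes in WP4.

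**Working it through.** **The plan's own figure.** 15 participants × 4 sites = 60, as stated. The article gives no precision or power basis for WP3, so nothing further can be reproduced.

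**Inputs.** From the article: n=60, Pearson for remote versus in-person, ICC for test-retest only. The article gives no SDs, error sizes or bias, so the following are assumptions for illustration: between-person SD 4 repetitions (variance 16), independent error SD 1.2 per mode (variance 1.44), and a constant remote undercount d of 0, 2 or 4 repetitions.

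**Step 1: Pearson r.** Each mode has total variance 16 + 1.44 = 17.44 and the covariance between modes is 16. Hence r = 16 / 17.44 = 0.917. The shift d does not enter, so r is 0.917 at all three values.

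**Step 2: absolute-agreement ICC (two-way, single measure).** For two modes, ICC = 16 / (17.44 + d²/2).

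**Step 3: limits of agreement.** The SD of the differences is 1.2 × √2 = 1.70, and 1.96 × 1.70 = 3.3. The limits are the bias ± 3.3 repetitions.

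| Undercount d | Pearson r | Absolute-agreement ICC | Limits of agreement (remote minus in-person) |
|---|---|---|---|
| 0 | 0.917 | 16/17.44 = 0.917 | −3.3 to +3.3 |
| 2 | 0.917 | 16/19.44 = 0.823 | −5.3 to +1.3 |
| 4 | 0.917 | 16/25.44 = 0.629 | −7.3 to −0.7 |

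**Step 4: the planned test-retest ICC.** If remote test and retest both carry the same shift, it drops out of their difference. Under the same assumptions the within-mode ICC is again 16/17.44 = 0.917 whatever d is.

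**Step 5: other assumed values.** In units of the in-person SD, with correlation ρ, remote-to-in-person SD ratio b and mean shift k, the ICC is 2ρb / (1 + b² + k²).
- With ρ = 0.9 and b = 1, it is 0.90, 0.87, 0.80, 0.60 and 0.42 for shifts of 0, 0.25, 0.5, 1 and 1.5 SD. Pearson r stays at 0.90.
- At a 1 SD shift, it runs from 0.53 (ρ = 0.8) to 0.63 (ρ = 0.95) with b = 1, and from 0.49 to 0.58 with b = 0.8.

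**Step 6: can 60 participants show a bias?** In 20,000 simulated studies with n=60, ρ = 0.9 and b = 1, mean Pearson r was 0.898 at every shift and always reached an illustrative cut-off of 0.75. The absolute-agreement ICC reached 0.75 in 100% of studies with no shift, 99.8% at 0.25 SD, 86% at 0.5 SD and 0% at 1 SD. A paired test of the mean difference detected a 0.25 SD shift with about 99% power. The planned sample can therefore reveal what Pearson r hides. The mean difference reveals it sooner than the ICC does.

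**The case against.** The strongest reply is that the article sets no cut-off or go/no-go rule, and that one clause in a condensed article does not make a high r sufficient for validity. That stands in part: a biased test could pass as valid, but nothing says that it would be declared so. The clause still assigns a specific, unsuitable statistic to the comparison, so this is more than a detail left for the analysis plan.

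Three stronger readings are tempting, and the documents do not support them.

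- **A reader might infer that WP4 will replace in-person scores with remote ones.** No section says this. The WP4 outcomes section has blinded physical therapists as assessors, the eligibility criteria require willingness to travel to the site for evaluations, and task T4.4 lists remote and clinical measures side by side. TUG and single-leg stance are not in the WP4 outcome list at all.
- **A reader might infer that the trial's treatment comparison is biased.** A constant shift cancels in change from baseline, and between arms, if everyone is measured in one mode. Bias that varies with disability or device need not cancel, but the article gives no evidence that such bias exists.
- **A reader might infer that the EDSS range of 2.5 to 6.5 inflates Pearson r in particular.** Between-person spread raises an ICC as well, and this is also the WP4 eligibility range. The point favours limits of agreement in raw units over any correlation-type coefficient.

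It is also fair that the shifts are assumed and the larger one is extreme. In the illustration, 2 repetitions still leave an ICC of 0.82. Misses that vary at random between people would lower r, so Pearson is not blind to every fault. Its blindness is to systematic shift and scale.

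**Conclusion.** The concern holds in a limited form. The only statistic named for remote versus in-person scores cannot detect a systematic difference between modes, and the planned ICC does not cover that comparison. A biased remote test could meet the RQ2 expectation of good validity on the stated method.

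That r ignores a constant shift or positive rescaling is mathematical and needs no assumption. The size of the gap does: r fixed at 0.92 against an absolute-agreement ICC of 0.92, 0.82 and 0.63 rests on SD 4, error SD 1.2 and undercounts of 0, 2 and 4 repetitions, none of which is in the article.

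The consequence falls on the RQ2 claim and on any use that treats remote and in-person scores as interchangeable. It does not extend to a WP4 between-arm comparison made wholly in one mode with a constant shift.

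**What to change.** Before WP3 is analysed, define the validity criterion for each of the five tests as:

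1. the mean remote minus in-person difference with its 95% CI;
2. Bland-Altman 95% limits of agreement in the test's own units;
3. a two-way, absolute-agreement, single-measure ICC with 95% CI.

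Judge these against an acceptable difference fixed in advance, or against the in-person test-retest error that WP3 will itself estimate. Do not rely on the ICC alone, since a moderate bias can leave it looking good. Keep Pearson or Spearman as a descriptive extra. Weighted kappa for the ordinal SPPB components is optional.

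The cost is small. The paired measurements are already planned, and no extra participants or visits are needed. There is somewhat more analysis and reporting, and the published validity figures may be lower than a correlation would have given.
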